### Plans for auditing trial conduct

Monitoring for this study will be performed by the sponsor and SCReN. Monitoring online visits will include, but not limited to, review of regulatory files, accountability records, CRFs, ICFs, medical and laboratory reports, site study intervention storage records, training records, and protocol and GCP compliance.

On-site and off-site monitoring, central review of data collection, and remote source data verification will be allowed according to EMA and AEMPS guidance/guidelines on the management of clinical trials during the COVID-19 (coronavirus) pandemic.

### Plans for communicating important protocol amendments to relevant parties (e.g., trial participants, ethical committees)

During the trial, any amendments to the protocol or consent materials will be approved by the REC before they are implemented.

### Dissemination plans

Following completion of the study, the results will be published in a scientific journal. Nevertheless, due to the critical need of results during the current epidemic COVID-19 crisis, preliminary results will be released by the sponsor to the Health Authorities.

### Ethical and regulatory

The clinical study will be conducted in accordance with the relevant national and international good clinical practice (GCP) guidelines, and the Declaration of Helsinki, each in the applicable version. The study protocol and the donors and the patients’ written informed consent were submitted to and approved by the Research Ethics Committee of Hospital Puerta de Hierro Majadahonda on March 23th, 2020.

## Discussion

COVID-19 is a respiratory disease caused by a novel coronavirus (SARS-CoV-2) and causes substantial morbidity and mortality. At the time the study protocol was designed, there were no vaccines to prevent COVID-19 or infection with SARS-CoV-2 or therapeutic agent to treat COVID-19. Indeed, as in any other health emergency, there was an enormous pressure to find cures and stop COVID-19 epidemic. This has prompted the extensive use of unproven treatments either on a compassionate use basis, in observational studies, or even in small clinical trials, but these do not provide the required level of evidence to solve the existing uncertainties. Thus, there was a substantial need to conduct appropriately powered randomized controlled studies in order to generate a reliable and conclusive evidence regarding the benefits and risks of these therapies.

In this scenario, convalescent plasma was hypothesized to be a potential therapeutic option given its extensively recognized immunomodulatory and anti-inflammatory effects. However, the actual benefits and risks of the intervention remain to be established, particularly in this novel condition. Currently, there are over 250 studies registered in ClinicalTrials.gov about convalescent plasma as a treatment for respiratory disease caused by COVID-19 all over the world, most of which are non-controlled clinical studies that are ongoing. Therefore, in accordance with the WHO Blood Regulators Network position statement [12] and our commitment to generate compelling evidence, we planned to conduct the proposed randomized and controlled trial to establish the effectiveness and safety of convalescent plasma from disease survivors in the treatment of patients with severe COVID-19 pneumonia.

This clinical trial is designed to evaluate passive immunotherapy with convalescent plasma for the treatment of adult patients hospitalized with non-severe COVID-19. With regard to the regulatory aspect, convalescent plasma from a single donor is not considered a medicinal product but rather it is subject to the regulation applicable to blood transfusions at the EU level. Subject to demonstration of its efficacy, it was considered that CP would constitute a universally accessible treatment option given that it relies entirely on already existing transfusions systems and technical requirements that are already established in every country. This makes CP a particularly attractive potential therapeutic option; even more considering that it is possible that the results of this study will contribute to the establishment of clinical recommendations to treat similar conditions.

The study was designed as an open-label study due to implications of a sham transfusion in the context of COVID-19 pandemic. The study was also designed as a controlled clinical trial. Initially, a three-treatment arm study including no experimental treatment (only SOC), unspecific standard plasma (plus SOC), and CP(+SOC) was considered. The aim was to demonstrate that any potential benefit from CP treatment was due to the presence of neutralizing antibodies and any other related cytokines released in a successful immune response and not just to the existing non-specific immune components in SARS-CoV-2 non-exposed donors. The inclusion of a third treatment arm with unspecific plasma might have also allowed ruling out any potential deleterious effect of transfusing an enriched plasma to a subject developing his/her own immune response. Nevertheless, a three-treatment arms trial was deemed unrealistic due to practical reasons and also to the well-known adverse events related to blood component transfusion, some of them even fatal, specially transfusion-related acute lung injury (TRALI).

Concerning the study population, a potential role of immunotherapy across the spectrum of COVID-19 disease has been suggested and several studies are ongoing to test different hypotheses. When defining the study population for our study, we considered that the best candidates for passive immunotherapy would be patients hospitalized due to COVID-19 pneumonia, thus in need for treatment, but early in the course of the disease when a primary immune response is not yet established. As a result, only patients requiring hospitalization for COVID-9 pneumonia without mechanical ventilation (invasive or non-invasive) or high flow oxygen devices, and with no more than 12 days between the onset of symptoms (fever or cough) and treatment administration day were allowed to enroll. It was believed that this early intervention would allow patients to benefit from the immune response of a subject who had developed a successful one, which might help clearing SARS-CoV-2 virus and to prevent progression to a more severe condition. On the other hand, patients requiring ventilation (mechanical or non-mechanical) were excluded given that they are less likely to respond to passive immunotherapy and more likely to develop ADE (antibody-dependent enhancement of disease), a worrisome complication seen previously in other viral infection [13] where a high specific antibody infusion could trigger a severe life-threatening immune response.

With regard to convalescent plasma donor’s selection, processing, and storage, it has been performed following the European and Spanish guidelines (RD 1088/2005) for standard plasma donation, including a pathogen reduction (PR) treatment. Lack of process control and standardization has been raised as one of the reasons why clinical trials have failed so far. We will select CP with anti SARS-CoV-2 IgG antibodies using a validated enzyme-linked immunosorbent assay (ELISA), with an IgG amount above a standardized cut-off. These assays have been performed at the trial central laboratory. No previous determination for neutralizing antibody titers will be used to select CP in our trial, as this would be the norm in the use of CP in the midst of a pandemic. Titration of neutralizing antibodies in the administered plasma will be subsequently performed and its relation to the outcomes could provide useful information about efficacy and safety of CP.

An important issue in our trial is that we selected our CP donors from recovered mild COVID-19 conditions. Although patients recovered from severe COVID-19 was not an exclusion criteria for donors in our trial, we chose mild donors based in two assumptions: first, severe patients could have a high anti SARS-CoV-2 IgG titer, but low neutralizing antibody titers; second, high neutralizing antibodies titers in CP could increase the risk of ADE (antibody-dependent enhancement of disease). Thus, our donor selection strategy is aimed to select CP with medium levels of antibody titers, which is thought to provide a fair balance of efficacy and safety.

CP will be administered as an add-on to the standard of care as defined in each study center. Based on the clinical practice recommendations in place at the time the study was designed, the standard of care could be based on any of the following: lopinavir/ritonavir, darunavir/cobicistat, hydroxy/chloroquine, tocilizumab. Remdesivir was added to standard of care once it was available outside clinical trials. Demonstration of efficacy in this context is particularly challenging, but ethical and feasibility issues were prioritized.

Defining the primary endpoint posed additional challenges given the existing uncertainties around the natural course of the disease, and the need to balance hard clinically relevant outcomes against outcomes that might occur earlier. The ordinal scale recommended by the WHO for clinical trials in COVID-19 was finally selected, as it was considered to provide a reasonable balance between these two criteria, while facilitating any external comparison with similar clinical trial outcomes. We also include a range of secondary endpoints to assess the scope of the disease and the potential benefits/risks of treatment in a broader spectrum, in an attempt to show consistency and the robustness of any potential effect shown in the primary endpoint.

Finally, to overcome practical difficulties due to paper handling limitations at COVID wards but to still comply with ethical requirements applied to clinical research, oral witnessed consent will be accepted before entering the trial. Written consent form will be obtained from the patient himself or acceptable representatives as soon as possible.

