**Methods/design:**

The ConPlas-19 study is a multicenter, randomized, open-label controlled trial. The study has been planned to include 278 adult patients hospitalized with severe COVID-19 infection not requiring mechanical ventilation (invasive or non-invasive). Subjects are randomly assigned in a 1:1 ratio (139 per treatment arm), stratified by center, to receive intravenously administered CP (single infusion) plus SOC or SOC alone, and are to be followed for 30 days. The primary endpoint of the study is the proportion of patients that progress to category 5, 6, or 7 (on the 7-point ordinal scale proposed by the WHO) at day 15. Interim analyses for efficacy and/or futility will be conducted once 20%, 40%, and 60% of the planned sample size are enrolled and complete D15 assessment.

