## Objectives

The trial objective is to evaluate the clinical efficacy and safety of Convalescent Plasma combined with standard of care (SOC) compared with SOC alone in adult patients with severe COVID-19.

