**Fig. 1 Fig1:**
[figure not shown]

[figure not shown]

[figure not shown]
SPIRIT 2013 Checklist: Recommended items to address in a clinical trial protocol and related documents*

Approximately 278 patients (139 per arm) with severe SARS-CoV-2 pneumonia will be enrolled at 32 centers. Individuals fulfilling selection criteria will be randomized to receive CP (+SOC) or SOC alone at a ratio of 1:1. Also, approximately 140–200 CP donors will be recruited.

The study has been planned with a sequential design. Interim analyses for safety monitoring and for comprehensive efficacy/futility will be conducted when 20%, 40%, 60%, and 80% of patients have been recruited and completed D15 primary endpoint assessment, or at the discretionary criteria of the Data Safety Monitoring Board (DSMB) when needed.

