### Eligibility criteria

#### Eligibility criteria for patients

*Inclusion criteria are as follows:*
Written informed consent prior to performing study procedures. Witnessed oral consent will be accepted in order to avoid paper handling, which increased the risk of transmission of the infection. Written consent by patient or representatives will be obtained as soon as possible.Male or female adult patient ≥ 18 years of age at the time of enrolment.Laboratory-confirmed SARS-CoV-2 infection as determined by PCR in naso/oropharyngeal swabs or any other relevant specimen obtained in the ongoing COVID-19 symptomatic period. Alternative tests (i.e., rapid antigenic tests) are also acceptable as laboratory confirmation if their adequate specificity has been accepted by the sponsor.Patients requiring hospitalization for COVID-19 without mechanical ventilation (invasive or non-invasive) or high flow oxygen devices and at least one of the following:- Radiographic evidence of pulmonary infiltrates by imaging (chest X-ray, CT scan, etc.) OR- Clinical assessment (evidence of rales/crackles on exam) and SpO2 ≤ 94% on room air that requires supplemental oxygen.No more than 12 days between the onset of symptoms (fever or cough) and treatment administration day. Following 31 August amendment, only patients with no more than 7 days between the onset of symptoms and treatment administration day are allowed for inclusion.

*Exclusion criteria are as follows:*
Requiring mechanical ventilation (invasive or non-invasive) or high flow oxygen devices at screening.More than 12 days since symptoms (fever or cough) onset.Participation in any other clinical trial of an experimental treatment for COVID-19.In the opinion of the clinical team, progression to death is imminent and inevitable within the next 24 h, irrespective of the provision of treatments.Any incompatibility or allergy to the administration of human plasma.Stage 4 severe chronic kidney disease or requiring dialysis (i.e., eGFR < 30).

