### Outcomes

#### Primary outcome measure

The primary outcome measure is the proportion of patients that progress to category 5, 6, or 7 (hospitalized severe disease or death categories) on the 7-point ordinal scale recommended in the Master Protocol of the WHO R&D Blueprint expert group, at day 15 (Table 1).

**Table 1 Tab1:** Ordinal scale for illness severity

1. Not hospitalized, no limitation of activities	
2. Not hospitalized, limitation of activities	
3. Hospitalized, not requiring supplemental oxygen	
4. Hospitalized, requiring supplemental oxygen by mask or nasal prongs	
5. Hospitalized, non-invasive ventilation or high flow oxygen	
6. Hospitalized, intubation and mechanical ventilation or ECMO	
7. Death	

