### Statistical methods

#### Statistical methods for primary and secondary outcomes

A detailed Statistical Analysis Plan (SAP) agreed upon by the CT Executive Board and the Project Statistician will be available early during the recruitment phase. This SAP will follow the general regulatory recommendations given in the ICHE9 (CPMP/ICH /363/96) guidance, as well as other specific guidance on methodological and statistical issues [8].

Likewise, it will stick to the recommendations given by the consensus documents of the scientific journals to improve reliability and value of medical research literature by promoting transparent and accurate reporting of clinical research studies.

The proportion of patients with failure, defined as category 5, 6, or 7 of the 7-point ordinal scale at day 15, will be estimated using a log-binomial regression model including stratification variables. In the unexpected event that the model does not fit, the Poisson regression model with long-link and robust variance estimator will be used instead.

Binary efficacy and safety outcomes will be analyzed as described for the primary endpoint.

Kaplan-Meier model will be used to analyze survival endpoints (TTF and OS). In all these analyses, in addition to the Kaplan-Meier curve, median, Q1, Q3, and their corresponding 95% CI, number of events, and censored case distribution will be shown. Group comparisons will be done using the (stratified) log-rank test and the (stratified) hazard ratios (HR) (95%CI) from the Cox model.

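### The article calls its population both severe and non-severe, while eligibility admits ordinal categories 3 and 4; the stated primary model does not name that baseline category as a covariate

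*Protocol article*

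**What the plan says.** **Label.** The Objectives compare plasma plus standard of care "compared with SOC alone in adult patients with severe COVID-19". Study design repeats the label: "Approximately 278 patients (139 per arm) with severe SARS-CoV-2 pneumonia will be enrolled at 32 centers". The Abstract's Methods/design paragraph has "278 adult patients hospitalized with severe COVID-19 infection not requiring mechanical ventilation (invasive or non-invasive". The Abstract's Background, the opening of the Discussion and the Conclusion also say severe. The next part of the Discussion says the trial is designed "for the treatment of adult patients hospitalized with non-severe COVID-19".

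**Eligibility.** Besides hospitalisation without ventilation or high-flow oxygen, a patient needs at least one of two findings. The first is "Radiographic evidence of pulmonary infiltrates by imaging (chest X-ray, CT scan, etc". The second combines crackles with low saturation that requires oxygen. The exclusion criteria repeat the bar on ventilation and high-flow devices.

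**Scale.** Table 1 separates hospitalised patients without oxygen (3), on mask or prongs (4), on non-invasive ventilation or high-flow oxygen (5), and intubated or on ECMO (6). The Primary outcome measure section describes categories 5 to 7 as "hospitalized severe disease or death categories", and Sample size does much the same.

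**Model.** The day-15 failure proportion "will be estimated using a log-binomial regression model including stratification variables", with a robust Poisson model as fallback. Sequence generation names centre as the stratification factor.

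**The concern.** Two neighbouring parts of the Discussion give opposite labels to the same trial. Severe also sits badly with the article's own description of categories 5 to 7, since patients in 5 and 6 are excluded and the primary endpoint is progression into that range. The objective tells a reader whom a result applies to, and here it does not match the entry criteria.

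The oxygen requirement appears only in the second eligibility option, so infiltrates alone admit a hospitalised patient who needs no oxygen. The sample therefore mixes categories 3 and 4, which start at different distances from category 5. The stated primary model does not use that difference, although it is plausibly prognostic and is recorded for other outcomes. At stake are a clear statement of the population and a modest amount of precision.

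**Working it through.** **1. Comparing the sections**

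| Place | Population |
|---|---|
| Abstract (Background; Methods/design), Objectives, Study design, opening of Discussion, Conclusion | severe |
| Discussion, following part | non-severe |
| Eligibility criteria | infiltrates alone, or crackles plus low saturation needing oxygen; no high-flow oxygen or ventilation: categories 3 and 4 |
| Primary outcome measure; Sample size | categories 5 to 7 described as severe disease or death |

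Trial status lists amendments to symptom duration, follow-up and antigen testing. None concerns severity, so the two labels are not an old and a new version.

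**2. Is baseline category available?** Yes. The secondary outcomes include change from baseline on the 7-point scale and time to improvement by one category from admission. Baseline clinical data are entered before randomisation (Concealment mechanism).

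**3. What adjustment would gain**

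Inputs from Sample size: 139 per arm, 20% versus 10%. The documents give no share or risk by category, so these are assumptions: *w* is the category 3 share, and *p3* and *p4* are the control risks, chosen so that *w·p3 + (1−w)·p4* = 0.20. Plasma halves the risk in both categories.

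- Between-category variance in the control arm: B = w(1−w)(p4−p3)². In the plasma arm it is B/4.
- Share of control-arm variance explained: B/0.16.
- Reduction in the variance of the risk difference at 20% versus 10%: 1.25·B/(0.16+0.09).
- SD of the between-arm imbalance in category share: √(2w(1−w)/139). Multiplying by (p4−p3) gives the shift in the crude risk difference at control-arm risks.
- Standard error of the crude risk difference: √(0.25/139) = 0.0424, or 4.24 points.

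| p3, p4, w | B | Control arm only | At 20% vs 10% | Imbalance SD | Shift (points) | Shift/SE |
|---|---|---|---|---|---|---|
| 0.10, 0.25, 1/3 | 0.0050 | 3.1% | 2.5% | 0.057 | 0.85 | 0.20 |
| 0.08, 0.28, 0.40 | 0.0096 | 6.0% | 4.8% | 0.059 | 1.18 | 0.28 |
| 0.05, 0.25, 0.25 | 0.0075 | 4.7% | 3.75% | 0.052 | 1.04 | 0.24 |
| 0.10, 0.30, 0.50 | 0.0100 | 6.2% | 5.0% | 0.060 | 1.20 | 0.28 |

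If plasma halves the risk and the two arms depart equally in opposite directions, the shift is multiplied by (1+0.5)/2 = 0.75. The largest value is then 0.75 × 1.20 = 0.90 points.

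**4. Wider range.** With a category 3 share of 10 to 50% and a category 4 risk two to four times the category 3 risk, the variance reduction is 0.5 to 7.2%. Unadjusted power at 139 per arm (fixed design, unpooled) is Φ(0.10/0.0424 − 1.96) = 65.5%; adjusted, it is 65.7 to 68.7%. That starting figure is below the stated 80%. The shortfall is a separate matter, and nothing here rests on it.

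**5. Check on the model's own scale.** Per stratum, Var(log RR) = [(1−p)/p + (1−q)/q]/n per arm, with q = p/2. In the last scenario the strata give 28/69.5 = 0.403 and 8/69.5 = 0.115. Pooled by inverse variance this is 0.0895, against 13/139 = 0.0935 unadjusted, a fall of 4.3%. The first scenario gives 28/46.33 = 0.604 and 10/92.67 = 0.108, pooled 0.0916, a fall of 2.1%. The order of size is the same as for the risk difference.

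**The case against.** The strongest reply is that the entry criteria, not an adjective, decide who is studied. They are explicit, the Discussion restates them, and the Abstract qualifies severe in the same sentence by excluding ventilation. Table 1 does not use the word, the article never defines it formally, and the Discussion elsewhere uses severity as a matter of degree. This stands: relabelling alone changes neither enrolment nor analysis. A reader might infer that the conclusions would be claimed for a population that was never studied, or that nobody enrolled counts as severe. The documents do not support that much. They show loose and contradictory wording around a population that is clearly fixed.

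On the model, the text says stratification variables are included; it does not say they are the only terms. A separate analysis plan is announced and may add covariates. This also stands, so the model point is an improvement on the method as stated and does not allege an omission. A reader might also infer that leaving out baseline category biases the primary estimate or inflates the type I error. It does neither in a randomised comparison. A chance imbalance of the size shown is ordinary sampling variation that the confidence interval already covers; setting 1.2 points against the 10-point target makes it look like bias.

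Finally, a covariate added after recruitment began, in an open-label trial with interim looks, is a change to the primary analysis and must be handled as one.

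**Conclusion.** The contradiction in the population description is plain from the text and should be resolved; by itself it is close to an editorial correction. The useful change to the analysis is to make baseline category a prespecified covariate. The benefit is modest: a variance reduction of roughly 0.5 to 7% over the range tried and 2.5 to 5% in the four central scenarios, worth at most about three percentage points of power at 139 per arm. A one-SD imbalance amounts to 0.2 to 0.3 of a standard error. All these sizes rest on assumed category shares and risks and on a constant halving of risk. If few category 3 patients enter, or their risk is close to that of category 4, the gain is near the lower end. The case for the change is that the information is already held and the adjusted analysis is easier to interpret for a mixed population.

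**What to change.** 1. Reconcile the Abstract (Background and Methods/design), Objectives, Study design, both parts of the Discussion and the Conclusion with the eligibility criteria. Describe the population as hospitalised adults not needing high-flow oxygen or ventilation (categories 3 and 4), and draw conclusions for that population.
2. In the statistical methods, add baseline ordinal category (3 versus 4) as a prespecified covariate in the primary log-binomial model, and equally in the fallback Poisson model.
3. Present the treatment effect by baseline category descriptively, without a separate claim in either.

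The cost is edited wording, one covariate and a descriptive table, with no extra data or patients. Because recruitment started in April 2020 and interim comparisons are planned, the covariate should be recorded as a dated change to the primary analysis before any further unblinded comparison. If the analysis plan already includes it, only the wording needs attention.
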